## Abstract

**Background:**

The benefits of virtual reality (VR)-based rehabilitation were reported in patients after stroke, but there is insufficient evidence about how VR promotes brain activation in the central nervous system. Hence, we designed this study to explore the effects of VR-based intervention on upper extremity motor function and associated brain activation in stroke patients.

**Methods/design:**

In this single-center, randomized, parallel-group clinical trial with a blinded assessment of outcomes, a total of 78 stroke patients will be assigned randomly to either the VR group or the control group. All stroke patients who have upper extremity motor deficits will be tested with functional magnetic resonance imaging (fMRI), electroencephalography (EEG), and clinical evaluation. Clinical assessment and fMRI will be performed three times on each subject. The primary outcome is the change in performance on the Fugl-Meyer Assessment Upper Extremity Scale (FMA-UE). Secondary outcomes are functional independence measure (FIM), Barthel Index (BI), grip strength, and changes in the blood oxygenation level-dependent (BOLD) effect in the ipsilesional and contralesional primary motor cortex (M1) on the left and right hemispheres assessed with resting-state fMRI (rs-fMRI), task-state fMRI (ts-fMRI), and changes in EEG at the baseline and weeks 4 and 8.

**Discussion:**

This study aims to provide high-quality evidence for the relationship between upper extremity motor function and brain activation in stroke. In addition, this is the first multimodal neuroimaging study that explores the evidence for neuroplasticity and associated upper motor function recovery after VR in stroke patients.

**Clinical trial registration:**

Chinese Clinical Trial Registry, identifier: ChiCTR2200063425.

## Introduction

A stroke, also known as a transient ischemic attack or cerebrovascular accident, occurs when a blood vessel suddenly ruptures or a blood clot becomes blocked, interrupting the supply of oxygen and nutrients to the brain tissue and causing brain tissue damage (1). The annual stroke mortality rate is ~1.57 million in China with a trend toward increasing stroke recurrence and mortality (2). The long-lasting residual impairments and upper extremity dysfunctions typically influence the daily activity and quality of life of a substantial number of stroke survivors. The prevalence of upper extremity impairment is present at ~50–80% in the acute phase (3) and 40–50% in the chronic stroke phase (4). The recovery of motor function in the upper extremities has a significant impact on the ability of stroke patients to live independently.

The field of neurological rehabilitation has begun to apply VR to improve the joint mobility, speed, and precision of extremities in post-stroke hemiplegia patients (5). Compared with conventional rehabilitation, the value of VR in the rehabilitation of motor dysfunction is creating an enhanced environment, facilitating task-specific training, and providing multimodal feedback to augment functional recovery (6). A meta-analysis of 2,470 stroke patients found that VR as an aid to upper extremity motor function helped improve upper extremity motor function and daily living ability (7). On this basis, by incorporating gamification features into rehabilitation, VR also helps to achieve an increased training dose, increased intensity, and increased patient compliance (8, 9). In addition, small sample studies have confirmed the effectiveness of VR as an adjunct to improving upper extremity motor function in stroke patients (9). At present, increasing research has paid attention to VR in the rehabilitation of upper extremity motor dysfunction after stroke and gradually applied brain neuroimaging technology to explore the mechanism of action, which is expected to make effective progress in the future (10).

Functional recovery after brain injury is largely dominated by neuroplasticity, which is a dynamic adaptation of the structure and function of the central nervous system throughout its life cycle (11). The connotation of neuroplasticity involves the axonal remodeling of cortical circuits and the rearrangement of cortical mapping that occurs with disorder recovery (12, 13). The current understanding based on neuroplasticity has important clinical significance for stroke rehabilitation research. The use of intensive, frequent, and obvious task-specific activities should be encouraged in order to support experience-dependent neuroplasticity and functional recovery. VR can enrich the training environment by participating in sensory, cognitive, and perceptual-motor pathways, and it is better able to provide the key components of neuroplasticity described above to support functional recovery outcomes than traditional rehabilitation interventions (14).

Vision is a powerful signal of the sensorimotor center, and visual motor training in virtual reality environments (VE) is based on stimulation of the motor processing system, which activates the lower cortex regions of the brain involved in the performance of the action. There is a rich intrahemispheric cortex–cortex projection relationship between the parietal occipital lobe and the movement-related frontal cortex associated with vision and spatial position (15), which verifies that the visual feedback that controls hand activity could be used to promote the activity of specific brain regions. VR technology is conceivable in terms of immersive and repetitive, intensive therapeutic exercises, and its mechanism of action in post-stroke motor dysfunction may be used to induce changes in neural substrates for restoration and compensation *via* diverse and interesting games (16). In addition, cortical recombination is involved in the recovery of motor function, and interspheric inhibition has been confirmed in the VR study of the upper extremities of stroke (17, 18). VR of the upper extremities can achieve a higher degree of cerebral cortical recombination than conventional rehabilitation training, that is, the activation of the laterality index in the healthy hemisphere decreased significantly after training and the activation of the laterality index in the affected hemisphere increased significantly (17).

Although many reviews of VR interventions have shown positive improvements in stroke rehabilitation, most studies have focused on the impact of VR intervention-based rehabilitation on the treatment of dysfunction, and only a few studies have focused on changes in the central nervous system in stroke patients under VR intervention. With high spatial resolution, fMRI might detect patterns of brain excitation during motor work or rest by using the blood oxygen level-dependent signal as an alternative indicator of neural activity, but the precision of fMRI is restricted. EEG technology detects electrical activity for the purposes of providing enhanced efficiency data and identifying critical neural substrates that underlie certain functional deficits. In the examination of patients with stroke, quantitative EEG measures demonstrated not only clinical value but also multidimensional repeatability and reliability (19). The use of multimodal neuroimaging to obtain more comprehensive, rich, accurate, and reliable brain information provides new monitoring means for the description of neural dynamic processes (20). Neuroimaging techniques could indirectly describe angiogenesis and neuroplasticity and provide quantifiable indicators and responses to therapeutic interventions for stroke (21). Synchronous EEG-fMRI could simultaneously collect electrophysiological and blood oxygen metabolism signals in brain activities, combining the advantages of the two, which not only provides the feasibility of fusion for the study of the two modes (22) but also provides a new means for understanding the description of neural dynamic processes, which plays an irreplaceable role. Therefore, the primary goal of this study is to explore the effects of VR intervention on upper extremity motor function and associated brain activation in stroke patients. Multimodal neuroimaging characteristics that could be used as indicators of a better response to VR were also investigated.

## Methods and analysis

### Design and setting

This is a prospective, randomized controlled trial conducted by the Second Hospital of Jiaxing. A total of 78 patients who meet the inclusion and exclusion criteria will be randomly divided into two groups. The intervention group will receive VR training and conventional rehabilitation treatment, and the control group will receive conventional rehabilitation treatment only. All treatments will be provided five times per week for 4 weeks. The primary outcome is the degree of restored upper extremity motor function, which is evaluated by the Fugl-Meyer Assessment Upper Extremity Scale (FMA-UE). Secondary outcomes are neuroimaging outcomes, which are measured by resting-state functional magnetic resonance imaging (rs-fMRI), task-state functional magnetic resonance imaging (ts-fMRI), and electroencephalography (EEG). All outcomes will be evaluated at baseline and weeks 4 and 8. The study's flow chart is shown in Figure 1. The Standard Protocol Items: Recommendations for Interventional Trials (SPIRIT) checklist (23) is detailed in an additional document available upon request (Supplementary material), and the schedule of this study is shown in Table 1.

**Figure 1 F1:**
[figure not shown]
Flow chart of the trial.

**Table 1 T1:** Process chart of the trial.

**Timepoint**	**Study period**			
	**Enrollment-1 week**	**Baseline 0 week**	**Treatment phase 4 weeks**	**Follow-up phase 8 weeks**
**Enrollment**				
Eligibility screen	✓			
Demographic	✓			
**Characteristics**				
Informed consent	✓			
Medical history	✓			
Merger disease	✓			
Randomization		✓		
**Interventions**				
Intervention group		✓	✓	
Control group		✓	✓	
**Assessments**				
FMA-UE		✓	✓	✓
FIM		✓	✓	✓
BI		✓	✓	✓
Grip strength		✓	✓	✓
rs-fMRI		✓	✓	✓
ts-fMRI		✓	✓	✓
EEG		✓	✓	✓

FMA-UE, Fugl-Meyer assessment for the upper extremity; FIM, functional independence measure; BI, barthel index; rs-fMRI, resting-state fMRI; ts-fMRI, task-state fMRI; EEG, electroencephalography.

### Recruitment of participants

This is the version of the protocol, dated 6 September 2022. Patients who meet the criteria will be recruited through outpatient and inpatient systems and advertisements. The recruitment began on January 2023 and is expected to end in December 2023. The trial registration number of the study is ChiCTR2200063425.

### Inclusion criteria

Participants who meet the following criteria are included:

(1) All meet the diagnostic criteria for stroke formulated by the 4th National Conference on Cerebrovascular Disease in 1995.(2) The ischemic cortical or subcortical stroke occurs for the first time.(3) The level of upper extremity motor function can execute at least four of the seven tasks in daily life as part of the Jebsen–Taylor test.(4) Age ≥ 18 years.(5) Normal hearing and vision and smooth communication.(6) No severe cognitive impairment and also mini-mental state examination (MMSE) with a score of 16 or above.

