### Exclusion criteria

Participants with the following conditions are excluded:

(1) Cerebral hemorrhage, subarachnoid hemorrhage, venous sinus thrombosis, transient ischemic attack, progressive stroke, or reversible ischemic attack.(2) Patients with a history of mental disorder or the use of antipsychotic medication or obvious suicidal tendencies.(3) Women who are pregnant.(4) Lesions located in both cerebral hemispheres, cerebellum, or brainstem.(5) Patients who have severe heart, liver, kidney, and other medical diseases or tumors.(6) Patients who have a history of metal implantation in the past and cannot cooperate with the MRI examination.

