### Randomization

The random allocation cards will be generated by an independent researcher using computer-generated random numbers. The qualifying patients who can be enrolled are then given the randomization sequence, which is then placed in secret, opaque envelopes.

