### Sample size

The objective of this study is to explore VR and conventional rehabilitation for upper extremity motor function after a stroke and to calculate the sample size by using G-Power (version 3.1) software. The effect size f is expected to be at least 0.25, and since the power is 0.80, the protocol should include 65 participants. Considering an expected 15% dropout rate, the sample size is increased to 78 participants.

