Research by Garcia et al. (36) showed that VR training effectively promoted the functional remodeling of the brain. Some studies have also found that VR training can activate the motor cortex, cerebellar cortex, and frontal white matter areas of the patient's contralateral side (37, 38). When completing virtual activities, visual and auditory feedback can enhance the motivation and focus of the participants, thereby improving the patient's attention and spatial perception function (39). By repeating the virtual activity task, the participants' motor learning ability and executive function can be strengthened (40). In addition, studies have confirmed that exercise training itself can also promote the recovery of cognitive function in patients after stroke, and the reason may be that exercise can promote the growth and survival of neurons in the affected side of the brain (41). A total of two studies reported clinical outcomes of improved upper extremity motor function after VR rehabilitation, with higher fractional anisotropy (FA) in the ipsilateral corticospinal tract (CST) and transcallosal motor fibers in a bilateral arm training study (42) and increased bilateral sensorimotor cortex and hippocampal gray matter volume in a constraint-induced movement therapy study (43). A previous study of patients with subacute stroke showed an initial decrease in FA in the ipsilateral CST and transcallosal M1–M1 fibers in the early post-stroke period (44).

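### Time since stroke is left open at entry and unused in the unadjusted FMA-UE comparison, which costs precision but does not bias the contrast

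*Protocol article*

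**What the plan says.** **Entry.** Item (2) of Inclusion criteria reads: "The ischemic cortical or subcortical stroke occurs for the first time". The other five inclusion items cover diagnosis, upper-limb ability on the Jebsen–Taylor tasks, age, hearing, vision and communication, and cognition. The exclusions touch on the course of the stroke only through "transient ischemic attack, progressive stroke, or reversible ischemic attack". Neither list sets a minimum or maximum time since onset.

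**Recruitment.** "Patients who meet the criteria will be recruited through outpatient and inpatient systems and advertisements".

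**Allocation.** Design and setting: "A total of 78 patients who meet the inclusion and exclusion criteria will be randomly divided into two groups". Randomization: "The random allocation cards will be generated by an independent researcher using computer-generated random numbers". Opaque envelopes follow. No ratio, block or stratification factor is named, and none is ruled out.

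**Analysis.** Data analysis compares FMA-UE between groups by a t-test or Mann–Whitney test, chosen on normality and equality of variance, and uses independent-sample t-tests for the secondary outcomes. The only covariates named are age and gender, in the fMRI paragraph.

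**Size.** Sample size states: "The effect size f is expected to be at least 0.25". With power 0.80 it arrives at 65 participants, raised to 78 for 15% dropout.

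**The concern.** The primary outcome is change in FMA-UE, measured at weeks 4 and 8. If patients soon after a stroke improve more over that period than patients long after one, whatever the treatment, part of the spread in change scores is explained by a variable known at enrolment. An unadjusted two-sample test leaves that part in the error term.

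The article does treat phase as relevant: its Introduction separates acute from chronic stroke, and its Discussion refers to patients at various stages. No stated design or analysis step uses it.

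Two things are at stake. One is the precision of the VR-versus-control contrast in a trial of 78. The other is how a result would be read if the arms happened to differ in time since stroke and no planned analysis took account of it.

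**Working it through.** **1. The plan's own figure.** For two equal groups d = 2f = 0.50. A two-group comparison at two-sided 0.05 and power 0.80 needs 128 patients in total by the noncentral-F calculation, not 65. (The 0.05 is from Data analysis; two-sided is assumed.) The figure of 65 appears only with inputs that the article does not state, for example a between-group repeated-measures test over three visits with correlation 0.25. The dropout step is fine: 65/0.85 = 76.5, so 77, or 66/0.85 = 77.6, so 78 with equal arms. With 33 per arm evaluable, the planned t-test at d = 0.50 has power 0.516. That low base is a separate sample-size matter and is not caused by stroke phase. It is only the reference point here.

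**2. Model for phase.** Let q be the share of early patients and D the early-minus-late difference in mean FMA-UE change, in within-phase SDs. The documents give neither, so both are assumed: q from 0.10 to 0.50 and D from 0.5 to 1.5. Take the within-phase variance as 1 and the same treatment effect in both phases.

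- Total variance: V = 1 + q(1−q)D²
- Effect size seen by the unadjusted test: 0.5/√V, if d = 0.5 is scaled to the within-phase SD

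**3. Power of the unadjusted test, 33 per arm** (0.516 without phase variation):

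| q | D | V | 0.5/√V | Power |
|---|---|---|---|---|
| 0.10 | 0.5 | 1.0225 | 0.494 | 0.51 |
| 0.10 | 1.0 | 1.09 | 0.479 | 0.48 |
| 0.25 | 0.5 | 1.047 | 0.489 | 0.50 |
| 0.25 | 1.0 | 1.1875 | 0.459 | 0.45 |
| 0.25 | 1.5 | 1.422 | 0.419 | 0.39 |
| 0.50 | 0.5 | 1.0625 | 0.485 | 0.49 |
| 0.50 | 1.0 | 1.25 | 0.447 | 0.43 |
| 0.50 | 1.5 | 1.5625 | 0.400 | 0.36 |

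A model with phase as a covariate removes q(1−q)D² from the error and spends one degree of freedom. Its power is 0.516 throughout.

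**4. The other scaling.** If d = 0.5 already refers to the SD of the enrolled mix, the unadjusted test keeps power 0.516 and nothing further is lost. Adjustment then raises the effective d to 0.5√V. At q = 0.10, D = 0.5 this is 0.5 × 1.011 = 0.506, with power about 0.525. At q = 0.50, D = 1.5 it is 0.5 × 1.25 = 0.625, with power about 0.705.

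**5. Chance imbalance is the same quantity.** With n per arm the variance of the unadjusted contrast is 2V/n = 2/n + 2q(1−q)D²/n. The second term is the variance due to the arms differing by chance in their early share. For n = 39, q = 0.5, D = 1 it is 0.5/39 = 0.0128, an SD of 0.113. The exact SD of the between-arm difference in early share, with 39 early patients among 78 split 39:39, is 0.114. A gap of 20 points or more has probability 0.07 in that setting. At D = 1 it would move the observed contrast by 0.2 SD, or 0.2/0.5 = 40% of d. The standard error of the unadjusted test already allows for such shifts.

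**The case against.** **Stratification is not shown to be absent.** Randomization is a two-sentence summary in a condensed article. It does not say that allocation is simple or unstratified, and such detail is commonly left to the full protocol. This stands. A reader might infer that allocation ignores stroke phase, but the text does not establish it. The point therefore rests on the stated between-group test, which would not use phase even if the list were stratified.

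**Covariate handling may also be only summarised.** Age and gender are said to be taken into account. That remark sits in the fMRI paragraph, though, and the test named for FMA-UE is a two-sample test without covariates. Time since stroke is named nowhere.

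**No bias arises.** A reader might infer that a chance imbalance in phase biases the VR effect, or is a second harm on top of the extra variance. Neither holds. Randomisation keeps the estimate unbiased and the type I error controlled, and the identity in step 5 shows that the imbalance is the extra variance.

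**The size is assumed.** This stands. The article gives no recovery rates by phase: the Introduction figures are prevalences of impairment. At a small early share and a small gap the loss is trivial. The Jebsen–Taylor requirement, the exclusion of progressive stroke and in-hospital treatment may narrow the mix further, although none of them defines phase.

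**Imaging arguments do not carry over.** The Discussion's remark on early white-matter change concerns fractional anisotropy, which is not an outcome here. Before–after fMRI tests within each group are open to natural recovery whether or not phase is stratified or adjusted between groups. Neither supports this point.

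**Conclusion.** The point holds as one of precision and interpretability. Entry is open on time since onset, the recruitment routes can produce a mixed population, and the stated FMA-UE test leaves phase variation in the error.

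Power falls from 0.52 to between 0.51 and 0.36, given an early share of 10–50%, a gap of 0.5–1.5 within-phase SD, 33 evaluable per arm, two-sided 0.05, and f = 0.25 scaled to the within-phase SD. Under the other scaling there is no added loss, only precision left unused. If enrolment turns out nearly uniform in phase, the effect is negligible either way.

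The documents do not support a claim of systematic bias, of an inflated type I error, or that broad eligibility is itself a mistake.

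**What to change.** 1. Keep eligibility as it is. Record the stroke onset date at enrolment with the medical history that Table 1 already schedules.
2. Before unblinding, replace the unadjusted FMA-UE comparison with a between-group ANCOVA that includes time since stroke and baseline FMA-UE. Fix in advance how time since stroke enters the model. Use the same covariate in the between-group imaging comparisons.
3. If the allocation list is not already stratified, stratify the remaining allocations by time since stroke, with one cut-point chosen by the sponsor and permuted blocks of concealed, varying size. If recruitment is complete, step 2 alone recovers most of the precision.

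Cost: one or two covariates and, if step 3 applies, two sets of envelopes to manage. No patients or visits are added.

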### Exclusion criteria

Participants with the following conditions are excluded:

(1) Cerebral hemorrhage, subarachnoid hemorrhage, venous sinus thrombosis, transient ischemic attack, progressive stroke, or reversible ischemic attack.(2) Patients with a history of mental disorder or the use of antipsychotic medication or obvious suicidal tendencies.(3) Women who are pregnant.(4) Lesions located in both cerebral hemispheres, cerebellum, or brainstem.(5) Patients who have severe heart, liver, kidney, and other medical diseases or tumors.(6) Patients who have a history of metal implantation in the past and cannot cooperate with the MRI examination.

### Randomization

The random allocation cards will be generated by an independent researcher using computer-generated random numbers. The qualifying patients who can be enrolled are then given the randomization sequence, which is then placed in secret, opaque envelopes.

### Blinding

Due to the nature of the VR training and the technical constraints, we are unable to undertake a double-blind study design. However, evaluators and statisticians of the outcomes will be unaware of the assignments. Patients will be treated independently to prevent communication, and only certified and experienced therapists will be allowed to conduct the VR training sessions. Therapists supply patients, evaluators, or statisticians with whatever information they may need on the allocation. An independent researcher will carry out analysis tasks during the data management and statistical analysis processes.

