### Outcome measures

Participants will be evaluated at baseline and weeks 4 and 8. All evaluations will be conducted by researchers who will be blinded to the treatment allocation.

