### Primary outcome

The primary outcome is the FMA-UE, which has been developed as an evaluative measure of the upper limb functionality recovery poststroke (25–27). The FMA-UE score is 66 points, with lower scores indicating more severely impaired UE and higher scores indicating better motor function improvements. The baseline assessment results of this study are recorded as FM0, the second assessment results are carried out as FM1 after interventions, and the follow-up assessment results are recorded as FM2.

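### The Blinding section contradicts itself: evaluators and statisticians are to be kept blind, yet therapists are to give them allocation information

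*Protocol article*

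**What the plan says.** The Abstract describes a "randomized, parallel-group clinical trial with a blinded assessment of outcomes". The Blinding section concedes that, given the nature of VR training, "we are unable to undertake a double-blind study design", and offers this safeguard in its place: "evaluators and statisticians of the outcomes will be unaware of the assignments". The Outcome measures section repeats the commitment: "All evaluations will be conducted by researchers who will be blinded to the treatment allocation".

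Two sentences after its own commitment, the Blinding section says: "Therapists supply patients, evaluators, or statisticians with whatever information they may need on the allocation".

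The outcome most exposed is the primary one: "The primary outcome is the FMA-UE, which has been developed as an evaluative measure of the upper limb functionality recovery poststroke". Under the Outcome measures section it is assessed by the study's evaluators at baseline and at weeks 4 and 8.

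**The concern.** The therapist sentence tells the people who know the arm to pass that knowledge to the people who are supposed not to have it. It is not a missing detail that a fuller protocol might supply. It is a positive statement in the methods, and it points the wrong way.

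The stakes come from the design. Therapists deliver either Wii-based training or upper-extremity exercises, and patients know which they receive, so neither group can be blinded. Protection against detection bias on the FMA-UE therefore rests mainly on the evaluator not knowing the arm. An evaluator who has been told cannot be made blind again, and neither sample size nor later analysis restores the blind.

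**Working it through.** No formula applies, and there is no plan figure to reproduce. The check is to set every statement about blinding side by side.

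| Place | Evaluators | Statisticians |
|---|---|---|
| Abstract, Methods/design | blinded | not mentioned |
| Blinding, statement of who is blinded | blinded | blinded |
| Outcome measures | blinded | not mentioned |
| Blinding, therapist sentence | receive allocation information | receive allocation information |

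1. **Same roles, same information.** The therapist sentence names evaluators and statisticians, as the commitment does, and its subject is the allocation. The two cannot be reconciled by saying they concern different people or different data. Patients are also named, but that part does no harm to blinding, since patients know their treatment anyway.

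2. **Is the sentence limited elsewhere?** Nothing confines it to emergency unblinding, to information other than the arm, or to the time after the database is locked. The sentence that follows it gives the analysis to an independent researcher, but does not say that this person is shielded from what therapists pass on.

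3. **Does the reference to need limit it?** One could argue that a blinded evaluator needs no allocation information, so that the sentence permits nothing. But the document does not say what counts as need or who decides. A statistician does need group labels to compare the arms, and the sentence makes the therapist the source of them, with no mention of coding.

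4. **Is there another instruction to therapists on this?** No. The section requires them to be certified and experienced, and has patients treated separately to prevent communication. No other sentence tells them what to do with their knowledge of the arm.

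5. **Does anything numerical change?** No. The 65 participants required and the 78 planned after allowance for dropout do not depend on this wording.

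The count is three statements for blinded evaluators against one that would unblind them. For statisticians it is one against one, within the same section.

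**The case against.** The strongest reply is that this is a language error. The sentence sits in a section written to describe blinding, three statements elsewhere say that assessment is blinded, and the article has other garbled wording; for instance, the FIM is described with the FMA-UE's score range and interpretation. A lost negation would explain the sentence completely. That is plausible, and it limits the finding: a reader might infer that blinded assessment has been cancelled, and the document does not support that. It explains the contradiction without removing it, because a therapist following the text as printed would disclose.

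Three further inferences are tempting and should not be drawn.

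- **Randomization.** That section says: "The qualifying patients who can be enrolled are then given the randomization sequence, which is then placed in secret, opaque envelopes". A reader might infer that patients see the sequence before it is concealed. The phrase can as well mean that patients are assigned a place in it, and the opaque envelopes show that concealment was intended. Further envelope procedure is detail that an article may leave to the full protocol.
- **EEG and choice of test.** A reader might infer that the visual rejection of EEG epochs, or the choice between the t-test and the Mann–Whitney test, would be steered by knowledge of the arm. The article does not say who rejects epochs, and it ties the choice of test to normality and equal variance. Such steering is conjecture.
- **Size.** A reader might want to express the bias as a share of the planned effect. The document gives no figure for rater bias, and its effect size f of 0.25 is not tied to a named test, so it cannot safely be converted into a difference between the arms.

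**Conclusion.** The concern holds as an internal contradiction that leaves the operative blinding rule unclear. The therapist sentence conflicts with the commitment in its own section, with the Abstract and with the Outcome measures section, and nothing in the document limits it. If it were followed, the FMA-UE raters, and the statisticians with them, would learn the arm in a trial that has no patient or therapist blinding to fall back on.

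The harm is conditional on the sentence having been acted on, which the document neither shows nor excludes. The size of any bias cannot be computed from it. The conclusion rests only on the wording of the four statements and on the FMA-UE being scored by the study's evaluators. It deserves correction despite being a probable slip, because it concerns who may know the arm when the primary outcome is scored.

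**What to change.** Replace the therapist sentence with: *Therapists will not disclose allocation to evaluators or statisticians; arms are coded A/B until the database is locked; any unblinding is recorded.*

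The article gives January 2023 as the start of recruitment, so correcting the text is not enough. The sponsor should confirm what therapists were actually told and, if allocation was passed on, record which assessments were affected.

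The key to the A/B codes should be held by someone other than the analyst. The article gives an independent researcher the task of generating the allocation and an independent researcher the task of analysis, without saying whether they are the same person; for coding to work, they must not be.

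The cost is one sentence, a reminder to therapists and a short check of the instructions already given. The sample size, visits and outcome measures do not change.
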